### Participant timeline {13}

Figure 1 demonstrates the participant timeline for this study. Participating audiologists will screen potential candidates in their normal day-to-day work. Signed consent and baseline assessment will be obtained from those who meet inclusion criteria and agree to participate in the study. All participants will have a 1-month follow-up after the initial assessment with an audiologist in-person or via telehealth where IOI-HA questionnaires will be administered, and HA data-logging will be accessed. Those in the intervention group will also undergo a 30-min one-on-one MI session after the 1-month follow-up visit and the details will be provided by the study coordinator. Subsequent follow-up visits will be conducted at 3, 6, and 12 months where participants will complete the IOI-HA questionnaire and their HA data-logging will be accessed.

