#### Intervention description {11a}

Patients allocated to the intervention group will attend a 30-min maximum one-on-one MI session hosted by a practicing MI therapist via Zoom at 1 month after the initial visit. Participants will also receive standard audiological care delivered at in-person clinic visits.

All control and intervention participants will be asked to attend 4 follow-up visits after the initial baseline assessment at 1, 3, 6, and 12 months. At follow-up visits, all participants will complete online International Outcome Inventory for Hearing Aids (IOI-HA) questionnaires and the study investigators will access each participant’s HA data-logging feature to determine the mean number of hours HAs were activated. Audiologist(s) will record the daily average hours of use based on the number of days since the last reading. All data will be entered using a secure online survey tool.

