#### Strategies to improve adherence to interventions {11c}

At each study visit, adherence to the study intervention will be assessed in both the intervention and control groups. Strategies to improve adherence include:Individual assessment and instruction by study investigators and those involved.Participants will be contacted directly by telephone by study investigators if there are missed visits to encourage continued participation and to evaluate/assess barriers that prohibit participation.Telehealth follow-up visits with participating audiologists will be offered to those who may have limited access or who prefer telehealth.

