#### Relevant concomitant care permitted or prohibited during the trial {11d}

There are no prohibitions on participants seeking or receiving unplanned care for HA malfunction or ear complaints during the course of the trial. All such visits and their purpose will be recorded.

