### Sample size {14}

Aazh et al.’s [6] feasibility investigation of assessing HA data-logged hours of use in response to MI concluded that a standardized difference of 0.6 was best for sample size estimation. Therefore to discern this difference or greater at a 5% significance level with a power of 80%, 45 patients will be required in each intervention arm based on Machin and Campbell’s [21] clinical trial design tables. Therefore, 90 participants in total at a randomization ratio of 1:1.

An allowance of 50% participant dropout rate was adopted in this study as opposed to the 20% drop out identified by Aazh et al. to compensate for the uncertainties or anticipated higher drop rate due to the COVID-19 pandemic [6]. This higher rate is reasonable because a previous hearing aid RCT trial conducted by our senior investigators who recruited participants from audiology clinics within the greater Vancouver area, in part over the pandemic period with 3 months’ follow-up, resulted in 39.1% of participant data in the intervention arm being unavailable because of participants’ failure to attend follow-up or complete study questionnaires fully [24]. This leads to an adjusted sample size of 180 participants, 90 per group.

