## Data collection and management

### Plans for assessment and collection of outcomes {18a}

Consented participants will be instructed about the study and its procedures. At the initial visit, data collection forms, including the email addresses of each participant, will be filled and collected by a trained audiology clinic assistant. This data will be securely stored on a password-protected device and transferred to the study coordinator and PI for long-term use and protection.

Outcome assessments of data-logged hearing hours and IOI-HA questionnaires will be performed at 1-, 3-, 6-, and 12-month time points after hearing aid fitting.

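### Hours and IOI-HA are collected at scheduled visits, with no stated way to obtain either after a missed visit, in a trial that allows for 50% loss

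*Protocol article*

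**What the plan says.** Intervention description {11a}, Participant timeline {13} and the 3-, 6- and 12-month part of Plans for assessment and collection of outcomes {18a} all place both outcomes at the follow-up visits, "where participants will complete the IOI-HA questionnaire and their HA data-logging will be accessed". The IOI-HA is completed online. For hours, audiologists "record the daily average hours of use based on the number of days since the last reading" ({11a}). Under {18b}, a clinic staff member fills in the forms together with the participant.

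The article also covers what happens off schedule:

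- **Telehealth.** It is an option for the 1-month visit ({13}) and is offered for follow-up visits to people with limited access or a preference for it ({11c}).
- **Missed visits.** Investigators telephone "to encourage continued participation and to evaluate/assess barriers that prohibit participation" ({11c}).
- **Unplanned visits.** For aid malfunction or ear complaints, "All such visits and their purpose will be recorded" ({11d}).

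Forms collected at the initial visit are described as "including the email addresses of each participant" ({18a}). Sample size {14} allows for 50% dropout. It cites an earlier trial in which 39.1% of intervention-arm data were unavailable through "failure to attend follow-up or complete study questionnaires fully". Section {20c} excludes participants whose hours or IOI-HA are missing or incomplete, while {18b} keeps and includes data collected before withdrawal.

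**The concern.** The investigators expect loss mainly because people miss follow-up or leave questionnaires unfinished. Every capture route in the article nevertheless depends on a scheduled visit, whether in person or by telehealth. When that visit is missed, neither of the two stated contacts is described as yielding an outcome, although the means exist: an online form, an email address, and a log that appears to run on between readings.

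What is at stake is precision and, through the exclusion rule in {20c}, who is compared. The trial studies adherence to the aid. It is plausible that people who miss visits also wear their aids less, and in that case recruiting more participants would not correct the selection. The documents do not establish this link.

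**Working it through.** **1. The plan's own figure.** Inputs from {14}: standardized difference d = 0.6 for data-logged hours, 5% significance, 80% power, 1:1 allocation. The article does not state sidedness.

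- Normal approximation, two-sided: n = 2(1.96 + 0.8416)² / 0.6² = 43.6, so 44 per arm.
- Two-sided t-test: 44.6, so 45 per arm, as stated. One-sided gives 35, which does not match.
- Inflation: 45 / (1 − 0.5) = 90 per arm, 180 in total, as stated.

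The sample size needs no correction.

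**2. What recovered log readings would add.** The documents do not say what share r of lost participants could be recovered, so r is an assumption. With 90 randomized per arm and 50% lost, the number analysed is n = 90 × [1 − 0.5(1 − r)] = 45(1 + r). Power is that of a two-sided t-test with noncentrality 0.6 × √(n/2). The standard error changes by the factor 1/√(1 + r).

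| r (assumed) | n per arm | Excluded | Noncentrality | Power | SE change |
|---|---|---|---|---|---|
| 0 | 45 | 50% | 2.846 | 80.4% | none |
| 10% | 49.5 | 45% | 2.985 | 84.0% | −5% |
| 20% | 54 | 40% | 3.118 | 87.1% | −9% |
| 30% | 58.5 | 35% | 3.245 | 89.6% | −12% |

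Rounding down to 49 and 58 per arm gives 83.6% and 89.3%.

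These figures concern hours only, because the 0.6 is for data-logged hours. An emailed IOI-HA supplies no hours and does not move this power. On its plain reading, {20c} requires both outcomes, so a recovered log reading returns a participant to the analysis only if the IOI-HA is also present or {20c} is amended.

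**3. How quickly missed visits accumulate.** Suppose incomplete in {20c} means any missed visit, and visits are missed independently (both assumptions). The share complete over four visits is (1 − m)⁴. With m = 10% per visit it is 65.6%; with m = 15.9% it is 50%, which is already the whole allowance.

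**4. What a late reading can replace.** If the 3-month reading is missed and the log is next read at 6 months, the average covers months 1 to 6. That is 2/5 × (mean for months 1–3) + 3/5 × (mean for months 3–6). Total use over the five months is recovered, provided the device keeps the log that long. The separate 3-month value is not.

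**The case against.** The strongest reply has five parts.

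- **Mitigation exists.** Telehealth follow-up is offered, so someone who cannot travel can still take part. This stands: a reader might infer that only in-person attendance yields data, and the article does not support that. The remaining gap concerns people who miss the visit in either mode.
- **Silence is not prohibition.** The article does not say that no outcome is taken on the call or at an unplanned visit, and a condensed article may leave such detail to the full protocol. This has some force. But the article does describe retention, missed visits and unplanned visits, and gives none of them an outcome reading.
- **The power gain is not shared by both remedies.** A reader might credit the emailed form with the 84% to 90%. It does not contribute to them.
- **A late reading is not a substitute visit value.** It averages a longer interval, may include a malfunction period, and shortens the interval behind the next scheduled average. This stands in full, so assigning any later reading to the nearest missed time point would be unsound. How long the log is kept and how it would be read remotely are also not stated.
- **Staff-assisted completion is deliberate.** Section {18b} uses it to secure complete forms, and an emailed form gives that up. This is a real but modest cost, since the alternative is no form at all.

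**Conclusion.** The point holds as a gap in data capture that is cheap to close; it is not an error in the sample size. As written, both outcomes depend on a scheduled visit, the stated responses to a missed or unplanned visit collect neither, and {20c} then excludes the participant.

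For hours, the gain would be from about 80% power to about 84%, 87% or 90% if log readings recovered 10%, 20% or 30% of those lost. That rests on an assumed recovery share, on the full 50% loss occurring, on the log being retained, and on {20c} not removing the participant for a missing IOI-HA. For the IOI-HA, the gain is completeness, which the documents give no basis to quantify. Its rank also varies: it is secondary in Outcomes {12} but listed as primary in the abstract and Table 2, so only the hours are certainly primary data.

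A reader might also infer that the planned loss will bias the comparison because non-attenders are low users. That is plausible, but nothing in the documents shows it. Nor can all of the 50% be regarded as recoverable, since it is a dropout allowance and people who withdraw may not be reachable by email or clinic contact.

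**What to change.** Amend {11a}, {11c}, {13}, {18b} and {20c} as follows.

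1. **IOI-HA.** When a 3-, 6- or 12-month visit is missed, including a telehealth visit, email the online link at the due date and mention it in the missed-visit call. Flag forms completed without staff.
2. **Hours.** Take a dated log reading at any clinic contact, including unplanned visits. Record the interval covered and any malfunction. Use the reading for a missed time point only within a pre-specified window. Compute each scheduled average over the full scheduled interval, weighting the sub-interval averages by their days, so that extra readings do not shorten it.
3. **Analysis set.** Reword {20c} so that a participant with one outcome available is analysed for that outcome, and reconcile it with {18b}, which retains and includes data collected before withdrawal.

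The cost is protocol wording, an automated email, and a reading at visits that take place anyway. The downside is that some readings fall off the nominal date and some forms are completed unassisted; the recorded interval and the flag allow both to be examined in the analysis.

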**Fig. 1 Fig1:**
[figure not shown]
Participants’ screening and randomization

### Sample size {14}

Aazh et al.’s [6] feasibility investigation of assessing HA data-logged hours of use in response to MI concluded that a standardized difference of 0.6 was best for sample size estimation. Therefore to discern this difference or greater at a 5% significance level with a power of 80%, 45 patients will be required in each intervention arm based on Machin and Campbell’s [21] clinical trial design tables. Therefore, 90 participants in total at a randomization ratio of 1:1.

An allowance of 50% participant dropout rate was adopted in this study as opposed to the 20% drop out identified by Aazh et al. to compensate for the uncertainties or anticipated higher drop rate due to the COVID-19 pandemic [6]. This higher rate is reasonable because a previous hearing aid RCT trial conducted by our senior investigators who recruited participants from audiology clinics within the greater Vancouver area, in part over the pandemic period with 3 months’ follow-up, resulted in 39.1% of participant data in the intervention arm being unavailable because of participants’ failure to attend follow-up or complete study questionnaires fully [24]. This leads to an adjusted sample size of 180 participants, 90 per group.

### Recruitment {15}

The estimated time period for recruitment, intervention, and data acquisition is 48 months. Investigating and collaborating with audiologists will invite eligible clients attending their clinics between January 2021 and December 2024 to participate in the study. The time requirement for participant recruitment and baseline assessment will be approximately 60 to 75 min.

## Assignment of interventions: allocation

### Sequence generation {16a}

Participants will be allocated to the study group by block randomization. The block sequence will be generated using the computer-generated STATA statistical package (Version 16). Block size variation will be used to prevent the prediction of treatment. Allocationwill be performed by the study coordinator who will not be involved in data collection; patients will be assigned a non-identifiable number sequence.

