### Trial design {8}

This study will be a multi-center, prospective, randomized patient-blind controlled trial and employ a between-subject, pre- and post-tests design with a treatment and control group. It has been designed to be a superiority trial assessing motivational interviewing compared to standard audiological care. The SPIRIT (Standard Protocol Items: Recommendations for Interventional Trials) reporting guidelines were used to develop the methodology.

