## Methods: participants, interventions, and outcomes

### Study setting {9}

Study participants will be recruited at audiology clinics located within the greater Vancouver region, British Columbia (BC), Canada. Audiology clinics will comply with WorkSafeBC and the Provincial Health Officer’s COVID-19 orders as related to safety plans. Audiologists will screen potential participants during the normal course of their work.

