### Interventions

#### Explanation for the choice of comparators {6b}

Participants in the control group will receive standard care as typically delivered by audiologists at in-person clinic visits with no additional treatment. Above comparator was selected to allow the effect of one-on-one MI on adherence to HA use to be compared with the current gold standard treatment of standard care. Audiologists will make treatment plans for new HA clients based on their personal experience, the evidence available from published studies, and expert opinion. There was no attempt to limit audiologists who deliver care in the comparator arm to ensure that the study outcomes can be generalized to the practice of non-study audiologists.

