### Concealment mechanism {16b}

As stated above, participants will be allocated to treatment or control groups using block randomization after being recruited by audiology clinics. Allocation will be done by the study coordinator in a sequentially numbered fashion using opaque, sealed envelopes. The study coordinator will only know one patient outcome of intervention at a time to inform the MI therapist and patient. The recruiting audiologists will be blinded to study group allocation and do not have access to the allocation sequence. Only the MI therapist and study coordinator will be informed of patient group allocation after recruitment.

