## Statistical methods

### Statistical methods for primary and secondary outcomes {20a}

Descriptive Statistics will be used to summarize patient demographics. Independent samples *T*-tests will be used to compare continuous variables such as PTA averages, word recognition scores, and data-logged hearing hours between groups. Chi-squared test will be used to determine the degree of association between categorical variables such as patient-reported outcome, sex, and age group. A univariate linear regression will be run with demographic variables and data-logged hearing hours. Pearson’s correlations will also be used to measure the strength of associations between data-logged hearing aid use hours and self-reported measures via the IOI-HA questionnaire. Data will be analyzed using SPSS (Version 25).

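### The stated t-test on data-logged hours leaves clinic out of a multi-centre trial with unrestricted local care; a clinic random intercept is a cheap, modest improvement in precision

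*Protocol article*

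**What the plan says.** **Design and setting.** Under Trial design {8}: "This study will be a multi-center, prospective, randomized patient-blind controlled trial". Under Study setting {9}: "Study participants will be recruited at audiology clinics located within the greater Vancouver region". The number of clinics is not given.

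**Local care.** Under Explanation for the choice of comparators {6b}: "Audiologists will make treatment plans for new HA clients based on their personal experience", and "There was no attempt to limit audiologists who deliver care in the comparator arm". The stated reason is generalisability. The intervention arm receives the same standard care plus one motivational interviewing session.

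**Allocation.** Sequence generation {16a} says "Participants will be allocated to the study group by block randomization" and "Block size variation will be used to prevent the prediction of treatment". Concealment mechanism {16b} adds: "Allocation will be done by the study coordinator in a sequentially numbered fashion using opaque, sealed envelopes". Neither section names clinic, or any other factor, as a stratum.

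**Analysis.** Statistical methods {20a} says that independent-samples t-tests "will be used to compare continuous variables such as PTA averages, word recognition scores, and data-logged hearing hours between groups". The only regression described is univariate, on demographic variables. Clinic does not appear.

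**The concern.** The design accepts variation between audiologists, and so probably between clinics, as the price of generalisability. Fitting practice and follow-up can then differ by clinic, and wear time with them. Clinic should be recorded for every participant, yet the stated comparison makes no use of it.

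The consequence depends on how the blocks were formed:

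- If they are not stratified by clinic, between-clinic variation sits in the error term of the t-test. The test is correct but less precise than it could be.
- If they are stratified by clinic, the arms are balanced within clinic but the t-test's standard error ignores that balance. It is then too large and the test is conservative.

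In both cases the remedy in the analysis is the same. At stake is some precision on the primary outcome, in a trial planned around 45 analysable participants per arm.

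**Working it through.** **Inputs from the protocol (Sample size {14}).** Standardised difference 0.6; 5% significance; 80% power; 45 per arm; 50% dropout; 180 in total.

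**Inputs assumed.** ICC for clinic 0 to 0.20; 5 to 10 clinics; total outcome SD set to 1, with the 0.6 standardised by the total SD.

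**Step 1: reproduce the plan's figure.**
- Normal approximation: n per arm = 2(1.960 + 0.842)²/0.6² = 43.6, so 44.
- Exact noncentral t, two-sided: 44 per arm gives power 0.795 and 45 gives 0.804. So 45 reproduces.
- Dropout: 90/(1 − 0.5) = 180. This reproduces.

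**Step 2: is the unstratified t-test valid?** Simulation with 90 analysable, 5 clinics and 4,000 runs per setting:

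| ICC | Type I error, t-test | Power, t-test |
|---|---|---|
| 0.05 | 0.054 | 81.2% |
| 0.10 | 0.044 | 81.4% |
| 0.20 | 0.048 | 81.9% |

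The nominal level and the planned power both hold.

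**Step 3: the most that removing clinic variation could give.** With all clinic variance removed and perfect balance, the residual SD is √(1 − ICC), the standard error is √(1 − ICC) × √(2/45), and the effective standardised difference is 0.6/√(1 − ICC). Power is from the noncentral t with 88 degrees of freedom.

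| ICC | SE (outcome SDs) | Effective difference | Power ceiling |
|---|---|---|---|
| 0 | 0.211 | 0.600 | 80.4% |
| 0.05 | 0.206 | 0.616 | 82.3% |
| 0.10 | 0.200 | 0.632 | 84.3% |
| 0.20 | 0.189 | 0.671 | 88.2% |

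These are the limits that stratifying and adjusting together can approach.

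**Step 4: gain from the analysis change alone (unstratified blocks).** Simulated power, t-test against random intercept, 1,200 runs per setting (simulation error about 1 point):

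| Clinics | ICC | t-test | Random intercept | Gain |
|---|---|---|---|---|
| 5 | 0 | 79.2% | 79.4% | 0.2 |
| 5 | 0.10 | 80.5% | 82.2% | 1.7 |
| 10 | 0.10 | 80.7% | 82.6% | 1.9 |
| 5 | 0.20 | 82.2% | 87.0% | 4.8 |
| 10 | 0.20 | 81.2% | 85.8% | 4.6 |

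A further simulation put the gain at ICC 0.05 at about 0.5 points and agreed with the rest.

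**Step 5: chance clinic imbalance.** With K equal clinics and unstratified allocation, the SD of the clinic-driven shift between arms is about √ICC × √(2/45) × √((K − 1)/K). For K = 5 this is 0.042, 0.060 and 0.084 outcome SDs at ICC 0.05, 0.10 and 0.20. Simulation gave about 0.04, 0.06 and 0.08. With stratified blocks it fell to about 0.01 to 0.02. The target difference is 0.6.

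**Step 6: if the blocks are already per clinic and the t-test is kept.** Simulated type I error with 5 clinics was 0.045, 0.036 and 0.029 at ICC 0.05, 0.10 and 0.20. As a check, under perfect balance the approximate level is 2Φ(−1.987/√(1 − ICC)) = 0.041, 0.036 and 0.026, which agrees in direction and size.

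**Step 7: fixed clinic effects.** With unstratified blocks at ICC 0.05, replacing the t-test by fixed clinic effects moved simulated power from 81.4% to 78.9% with 10 clinics, and from 81% to 75% with 15. Many small clinics make fixed effects a poor choice.

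**The case against.** The strongest reply is that nothing is wrong: the t-test keeps its level, the planned power is met, the estimate is unbiased in expectation, and the sample size reproduces. That stands, and it limits the point to efficiency. It does not remove the point, because the article names the test for hours and that test cannot carry clinic. This is a stated choice, not a detail left to a fuller document.

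A second reply is that the article is condensed and does not say the blocks are unstratified. This also stands. A reader might infer one sequence running across all clinics from the single coordinator and the numbered envelopes. Central allocation is equally compatible with a series per clinic, so the text supports only the statement that no stratum is named.

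A third reply is that the gain rests on an ICC and a clinic count that the documents do not supply, with all clinics in one metropolitan region. It stands: at ICC 0.05 or below the gain is under one point.

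Two stronger readings are tempting and should be resisted:

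- One might say that part of any observed difference would be owed to which clinics fed each arm. Under unstratified randomisation that chance component is already in the t-test's standard error, and Step 5 shows it is small beside 0.6. A clinic of 20 among 180 would indeed have a 9.5% chance of a 14:6 split or worse (hypergeometric), but the clinic size is invented and the split alone says nothing about the estimate.
- One might claim power above 85% at ICC 0.10, or of 90% at ICC 0.20, once blocks are stratified. Those values exceed the ceilings in Step 3 and can only be simulation error.

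**Conclusion.** The point holds as a cheap improvement of modest severity. The article describes a multi-centre trial with unrestricted local care and specifies a primary comparison that ignores clinic. Validity, type I error and the stated power are intact if the blocks are unstratified; if they are stratified by clinic, the plain t-test is conservative.

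The analysis change alone is worth about 0 power points at ICC 0, under 1 at 0.05, about 2 at 0.10 and 4 to 5 at 0.20. Adding stratification can bring power to at most about 84% at ICC 0.10 or 88% at ICC 0.20. All of this assumes 45 analysable per arm, 5 to 10 clinics, and 0.6 standardised by the total SD. The documents give no ICC, so they do not show where in this range the trial lies.

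**What to change.** 1. In Statistical methods {20a}, replace the t-test on data-logged hours by a linear mixed model with arm and a random intercept for clinic, fixed in writing before outcomes are seen. It applies to everyone already randomised, and specifying it early prevents a data-driven choice about clinic later.
2. In Sequence generation {16a}, state whether the blocks are formed per clinic. If they are not and recruitment is still open, use a separate varied-block sequence per clinic for the remaining participants. Trial status expects recruitment to end in December 2023, so this part may reach few people or none.

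**Cost.** A sentence of analysis text and one extra variance component, plus per-clinic envelope sets if step 2 applies. Avoid fixed clinic effects if there are many small clinics.
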